### Specific Aim 2– To evaluate the kinematic and kinetic differences of non-articulating ESR, articulating ESR, and active plantar flexion ESR feet in individuals with transtibial amputation

Hypothesis 2.1 Plantarflexion forces (i.e. ground reaction forces) at push off /terminal stance will be most symmetrical to the intact limb for active plantarflexion devices, followed by non-articulating ESR feet, and lastly articulating ESR devices.

Hypothesis 2.2 Biomechanical symmetry in gait while negotiating a decline will be greater for both active plantarflexion ESR and articulating ankle ESR conditions compared to non-articulating ESR feet.

Hypothesis 2.3 Biomechanical symmetry in gait while negotiating an incline will be greatest for devices with active plantarflexion, followed by articulating devices, and lastly non-articulating ESR feet.

Hypothesis 2.4 Ambulation at a faster than self-selected walking speed will yield decreased symmetry in articulating ankle ESR and non-articulating ESR feet but not with the active plantar flexion ESR feet.

Hypothesis 2.5 Articulating ESR feet will not yield significant differences in gait symmetry regardless of specific foot assigned within the articulating ESR category.

**Specific Aim 3 – To correlate biomechanical findings with functional and subjective outcome measures and with user preference determined through activity monitoring and user satisfaction to develop guidelines for appropriate prosthetic prescription.**

Hypothesis 3.1 Individuals that commonly negotiate ramps, hills, inclines or declines will show preference for an articulating ankle ESR and/or active plantarflexion ESR feet over non-articulating ESR feet

Hypothesis 3.2 Individuals that have higher step counts, but do so at a low activity level will prefer the active plantarflexion ESR ankle-foot prosthesis.

Hypothesis 3.3 The majority of subjects will chose to utilize a single prosthesis for all activities, and not use different prostheses for different activities, as measured through step activity monitoring and daily activity logs.

Hypothesis 3.4 Step activity performance will, and age will not, correlate with prosthetic feet category that best optimizes function.

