## **Part 1a: Screening, Consent, Enrollment, Prosthetic Socket Assessment**

During the first visit, subjects will be screened according to the inclusion/exclusion criteria, consented and enrolled. Demographic information will be collected including, age, height, weight, injury etiology, and time as a prosthesis user. Fit and comfort of each subject's existing socket will be evaluated by the study prosthetist on-site through standardized prosthetic guidelines. Once fit and comfort are confirmed, the study prosthetist will create a mold using plaster of paris or alginate for fabrication of two identical prosthetic sockets.

Between visits 1 and 2, the molds of the existing socket shape and volume will be used to create laminated, definitive sockets, for the two additional prostheses. These sockets will be centrally fabricated at VANYHHS. The same materials as used in the subject's current socket will be used to create each additional socket to eliminate any variance in perceived weight or socket flexibility. Each additional socket will be aligned/programmed with a designated prosthetic foot to manufacturer's specifications by the study prosthetist.

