#### Development of Prediction Model:

In order to develop guidelines for prosthetic prescription of ankle-foot devices, the goal of this proposal is to determine which factors and outcomes are most predictive of optimal performance to meet patient goals. To do this, initial analyses will consist of bivariate cross-tabulations, conducted using chi square analyses, based on clinical hypotheses between each potential explanatory variable. Variable selection for the multivariate model will be informed by bivariate findings. Logistic regression will then be performed with patient preference of prosthesis regressed on each of several domains (i.e. functional levels/outcomes, Activity levels, biomechanical parameters, among others). The models will control for multiple variables simultaneously. The C-statistic corresponding to the area under the receiver operating characteristic (ROC) curve will be used to assess overall predictive value. Theory-driven domain specific models (based on bivariate findings) and one parsimonious stepwise logistic regression model combining the domains will be created. This will help determine whether each distinct component predicts optimal prosthetic prescription outcome. Each domain-specific model will be adjusted for and controlled for confounding factors. The individual variables expressing the components of each domain will be entered as fixed predictors. Finally, a stepwise multiple regression will be applied to identify the set of clinical factors that represent the strongest independent predictors. The stepwise regression will be conducted through a series of domain-specific forward-regression models and one backward regression. The variables significant in these forward selection models will be placed in the backward model and will be removed at  $P = .10$ . The significant variables from the backward regression will be presented as the strongest independent predictive factors and be used to help guide prosthetic prescription.

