#### Power Analysis:

| Site                                                | n   | n for subset |
|-----------------------------------------------------|------------|---------------------|
| VA New York Harbor Healthcare System (NYC)          | 30         | 15                  |
| Walter Reed National Military Medical Center (D.C.) | 30         | 15                  |
| VA Puget Sound Healthcare System (Seattle)          | 30         | 0                   |
| James J. Peters VA Medical Center (Tampa)           | 30         | 0                   |
| TOTAL                                        | 120 | 30           |

Figure 7. Total Subjects per site to be seen over the course of 3 year period

#### Specific Aim 1

Functional measures will be analyzed by multilevel (site) repeated measures analysis of variance. Because order of prosthesis will be randomized, there should be no order effect. However, order will be included in the initial analysis to test this assumption. Assuming an alpha error rate of 5% and within-group standard deviation of 5, 120 subjects will provide over 98% power to detect a 3 unit difference between at least two of the ESR groups for each of the functional measures.

### Specific Aim 2

Kinematic and kinetic measures will be analyzed by multilevel (site) repeated measures analysis of variance. Because order of prosthesis will be randomized, there should be no order effect. However, order will be included in the initial analysis to test this assumption. Assuming an alpha error rate of 5% and within-group standard deviation of 10, 30 subjects will provide 72% power to detect a 6-unit difference between at least two of the ESR groups for each of the measures.

### Specific Aim 3

This analysis will be performed using paired t-test to determine correlations between prosthesis chosen as per SAM data and which functional outcome measures are indicative of that choice. Additionally pair t-test will be performed between kinematic and kinetic data to again correlate with the prosthetic choice of the subject as demonstrated through the SAM data. Finally all SAM data will be evaluated against the activity journal to determine the roll of a specific activity goal and a specific prosthesis.

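### Hypothesis 3.4 predicts that age is unrelated to the best foot category, but the Aim 3 methods can only fail to detect an age association and cannot support its absence

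*Protocol*

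**What the plan says.** Under Specific Aim 3, Hypothesis 3.4 reads: "Step activity performance will, and age will not, correlate with prosthetic feet category that best optimizes function". It pairs a predicted association (step activity) with a predicted absence of one (age).

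Age is recorded once, at enrolment (Part 1a): "Demographic information will be collected including, age, height, weight, injury etiology, and time as a prosthesis user". No Aim 3 analysis names it.

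The methods appear in two places. Under Development of Prediction Model, "initial analyses will consist of bivariate cross-tabulations, conducted using chi square analyses". Bivariate results then inform which variables enter the multivariable model. Logistic regression of prosthesis preference follows, by domain, and then forward selection and a backward step with removal at P = .10. The section concludes: "The significant variables from the backward regression will be presented as the strongest independent predictive factors". A C-statistic describes the predictive value of the model as a whole. Under Power Analysis, Specific Aim 3, "This analysis will be performed using paired t-test to determine correlations between prosthesis chosen as per SAM data". That paragraph gives no effect size, power or margin.

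**The concern.** A non-significant result means that the data did not rule out zero. It does not show that the true value is near zero. Each inferential step named for Aim 3 either rejects a null hypothesis or fails to, and the selection procedure ends by presenting the variables that survived. If age does not survive, the natural reading beside Hypothesis 3.4 is that the prediction came true, although the data may be compatible with an association worth knowing about.

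The study exists to produce prescription criteria and material for practice guidelines. An algorithm that leaves age out because age was shown not to matter differs from one that leaves it out because its effect was not detected. The analysis as written does not tell the reader which of these applies.

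**Working it through.** **Inputs.** n = 120 (Power Analysis table; no dropout allowance is stated, so this is a best case). Alpha of 5% is stated for Aims 1 and 2 only, without sidedness; two-sided is assumed. P = .10 is the backward-removal level. The protocol gives no size for an age association and no margin, so the sizes below are assumptions shown as a range.

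**The plan's own figure at this sample size.** For Aim 1: "Assuming an alpha error rate of 5% and within-group standard deviation of 5, 120 subjects will provide over 98% power". The target there is a gap of 3 units on a functional measure. For a three-condition repeated-measures ANOVA with means 0, 1.5 and 3, SD 5 and zero within-subject correlation, the sum of squared deviations is 2 × 1.5² = 4.5. The noncentrality is 120 × 4.5 / 25 = 21.6. On 2 and 238 degrees of freedom the power is 99.0%, so the stated figure reproduces. It concerns differences between feet and says nothing about age.

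**Chance of missing an age association (correlation approximation).** Fisher's z has standard error 1/√(120 − 3) = 0.0925. For a true correlation r, the standardised shift is atanh(r)/0.0925. The chance of non-significance is Φ(c − shift) − Φ(−c − shift), with c = 1.96 at 5% and 1.645 at 10%.

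| True r | Shift | Non-significant at 5% | Non-significant at 10% |
|---|---|---|---|
| 0.15 | 1.635 | 63% | 50% |
| 0.20 | 2.193 | 41% | 29% |
| 0.25 | 2.763 | 21% | 13% |
| 0.30 | 3.348 | 8% | 4% |

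**What a null result leaves open.** With an observed r of zero, the 95% interval is ±tanh(1.96 × 0.0925) = ±0.18. An observed r just short of significance (about 0.18) has an upper limit of tanh(2 × 1.96 × 0.0925) = 0.35.

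**Closer to the planned outcome.** Preference is a choice among three foot categories. For one category against the rest, the log odds ratio per SD of age has approximate standard error 1/√(120·p(1 − p)). For an assumed category share p of 50% this is 0.183; for 20% it is 0.228. An observed odds ratio of 1 then has a 95% interval of 0.70 to 1.43 (share 50%) or 0.64 to 1.56 (share 20%). A true odds ratio of 1.5 per SD would be non-significant at 5% in about 40% to 57% of trials across those shares.

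**Can the named steps support absence?** Chi-square screening, forward entry and backward removal turn on p-values. The C-statistic rates the whole model and does not isolate age. A paired t-test compares two measurements on the same subject. Age has one value per subject, so that test cannot address it.

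**Would a correlation margin of ±0.30 help?** Requiring the 90% interval to lie inside ±0.30 accepts absence when the observed |r| is below tanh(atanh(0.30) − 1.645 × 0.0925) = 0.156. The P = .10 rule drops age when |r| is below tanh(1.645 × 0.0925) = 0.151. The two cut-offs are almost the same. At true r of 0.15, 0.20 and 0.25 that margin accepts absence in 53%, 31% and 14% of trials, against 50%, 29% and 13% for the P = .10 rule. Margins of 0.25 and 0.20 are stricter, but when the true value is zero their power at n = 120 is 74% and 42%.

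**The case against.** The strongest reply is that the protocol never says a dropped variable will be declared irrelevant. That is correct. There is no decision rule for Hypothesis 3.4, and a reader who infers that non-significance will be reported as confirmation goes beyond the text.

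It is also fair that the plan contains more than stepwise selection. The domain-specific models enter their variables as fixed predictors and adjust for confounders, so age might be retained there. The protocol does not say that it will be, and it plans no interval or other statement about age in those models.

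A reader might further infer that a moderate age association would probably be missed. On the correlation scale this fails: r = 0.30 is missed only about 8% of the time at 5%. The exposure is to small-to-moderate associations, or to a nominal outcome with uneven category shares.

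Hypothesis 3.4 refers to the category that optimises function, whereas the model predicts preference, so it is not certain that this model is the intended test. No other analysis of age is offered, however.

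Finally, a margin or an interval criterion is commonly left to the SAP, which is not shown. Its absence is therefore not the point. The point is that the protocol predicts an absence and itself fixes a method that cannot support one; an SAP that followed the protocol would inherit the problem.

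**Conclusion.** The concern holds in a limited form. As written, the Aim 3 analyses can fail to find an age association but cannot support the age half of Hypothesis 3.4. With 120 subjects, true correlations of 0.15 to 0.25 would go undetected in about 63% down to 21% of trials at 5%, or 50% down to 13% at P = .10. Even an observed zero leaves about ±0.18.

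These figures use a correlation as a stand-in for association with a three-category choice, a single test and no dropout. The effect sizes and category shares are assumptions. The documents do not establish that the investigators will treat non-significance as proof, nor that large age effects would be missed.

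This is half of one hypothesis in the last aim, so the weight is modest, but it bears on the prescription criteria. The logical point also applies to Hypotheses 1.4, 1.5 and 2.5, which predict no significant differences within foot categories; the figures above do not carry over to them.

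**What to change.** - Keep age in the Aim 3 preference model whatever its p-value. Report its association with a 95% interval, for example as odds ratios per SD or per 10 years for each foot category.
- State that neither non-significance nor non-selection will count as support for the age half of Hypothesis 3.4.
- Then choose one of two routes. Either reword that half as exploratory, or accept it only if the interval lies inside a margin that is set and justified in advance on the scale of the planned model. A correlation margin of ±0.30 is a poor choice, because it accepts absence about as often as the P = .10 rule drops age.
- Apply the same reporting principle to Hypotheses 1.4, 1.5 and 2.5.

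The cost is wording in the protocol or SAP and one retained model term, with no added subjects, visits or data. The drawback is that the age result may have to be reported as inconclusive.

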### **Research Design:**

This investigation will be a prospective multi-center study, including the VANYHHS, VA Puget Sound Healthcare System (Seattle VA), James A. Haley VA Medical Center (Tampa VA), and Walter Reed National Military Medical Center (WRNMMC). All sites currently have access and have conducted research on the targeted population. Recruitment of subjects will be done through IRB approved methods.

### **Inclusion Criteria:**

- Veteran or Service Member with unilateral TTA
- Subject uses a prosthesis with a well-fitting socket for a minimum of one month
- Each subject must be able to achieve a “No Helper” score on the Functional Independence Measure (FIM) for the 3 mobility items (locomotion, transfers, stairs)

### **Functional Independence Measure for Inclusion:**

All subjects must be able to achieve a minimum score of a “modified independence” for the 3 mobility items.

Locomotion: Must be for minimum walking score of “modified independence”. A subject may use a wheelchair part time, but FIM inclusion criteria for locomotion must be specifically for “walking” or “both”.

### **Exclusion criteria:**

- subjects with active wounds/ulcers or significant musculoskeletal comorbidities on their intact limb that would impair their ability to participate in all functional outcome measures
- subjects with knee flexion contracture > 5 degrees
- any comorbidity that results in rapid limb volume changes (i.e. end stage renal disease with dialysis),
- a poorly fitting socket
- cognitive deficit(s) or mental health pathology limiting a subject’s ability to participate fully in the study
- subjects who are unable or unwilling to comply with all research visits
- women who are pregnant or who plan to become pregnant in the near future
- subject weighs more than product weight load maximums
- score of less than “modified independence” on any of the FIM mobility items

### **Foot Selection:**

Prosthetic ankle-foot units included in this study will be grouped in to three categories: 1) Non-articulating ESR - this group will be any qualifying ESR ankle-foot unit that is commercially available. This will typically be the foot the subject is currently using. This group contains over 100 commercially available prosthetic feet, and will be randomly chosen from all available options that fit the subject’s anatomy if the user does not current have a non-articulating ESR foot. 2) Articulating ESR – this group includes all commercially available options

that have an articulating ankle and also have ESR qualities, currently Endolite Echelon, Fillauer Motion Foot, Freedom Innovations Kinterra, Endolite Elan, Ossur Propriofoot, Hosmer Raize, Otto Bock Triton Smart Ankle, and Ossur Proflex (Figure 2) meet this criteria. 3) Active (Powered) Plantarflexion - the third group will contain all commercially available ESR ankle-foot units with active plantarflexion. Currently, the iWalk BiOM is the only foot that would be classified into the Active Plantarflexion ESR group. If new prosthetic feet-ankle units become commercially available during the course of this study, they will be added to the appropriate groups.

#### Justification for inclusion of all commercially available feet

*Non-articulating ESR Group:* Many non-articulating ESR prosthetic feet have different mechanical features (i.e. torsion, vertical shock) that provide for specific HCPCS code classification as explained in AOPA's "Prosthetic Foot Project" (24). However, to the best of our knowledge, while there may be subtle mechanical differences between these feet, no studies to date have shown any significant differences in impact on function between different non-articulating ESR feet. More specifically, while manufacturer marketing and patient subjective feedback can often report differences between prosthetic feet, there are no published differences in function during level ground ambulation, stair negotiation, or incline/decline ambulation using non-articulating ESR feet (10-12). Clinical consensus is that patients do have individual preferences for specific non-articulating ESR ankle-foot units, but there is no current metric(s) to predict this. To limit the study to one, or just a few non-articulating ESR feet, would limit the findings to just that one or a few specific feet chosen to represent a large group when drawing a conclusion. Additionally, most patients seen at the sites included in this study have the ability to trial many different prosthetic feet, as prescription is not driven by reimbursement rates within VA or DoD, and thus the foot the subject enrolls with may be a foot of preference within the larger non-articulating ESR category. Prosthetic feet frequently change, update, and can even be taken off the market for another generation ankle-foot unit. Limiting the foot choices, would also run the risk of not investigating the current trends of what is being prescribed in the amputation care clinics at the four VA and DoD sites in this study.

*Articulating ESR Group:* The articulating ESR group contains mechanical and microprocessor controlled prosthetic ankle-foot units. While there is research comparing these devices to SACH feet and non-articulating ESR feet, there is no current research suggesting any differences between the feet within this group in their effect on functional performance. These prosthetic ankle-foot units have articulation ranges from 9 to 50 degrees within this group, and it has been reported that average range of motion in a healthy individual with an intact lower limb is 20-40 degrees for ankle plantar/dorsiflexion (25). There is no published research to-date as to the ideal range of motion for an individual with transtibial limb loss, so all ankle-foot units will be included. Internal analysis within all groups will be conducted at the completion of this study to substantiate or rebut these groupings, and to determine if there are in fact outliers that should be classified differently clinically or in future research.

*Active Plantarflexion ESR Group:* Criteria for this group includes the following

- Commercially available
- Must be articulating
- Provides plantarflexion energy during terminal stance at a rate that is greater than the total energy absorbed (i.e. >100%)

#### Research Protocol:

Figure 6 – Project timeline for each subject.

[figure not shown]

## **Part 1a: Screening, Consent, Enrollment, Prosthetic Socket Assessment**

During the first visit, subjects will be screened according to the inclusion/exclusion criteria, consented and enrolled. Demographic information will be collected including, age, height, weight, injury etiology, and time as a prosthesis user. Fit and comfort of each subject's existing socket will be evaluated by the study prosthetist on-site through standardized prosthetic guidelines. Once fit and comfort are confirmed, the study prosthetist will create a mold using plaster of paris or alginate for fabrication of two identical prosthetic sockets.

Between visits 1 and 2, the molds of the existing socket shape and volume will be used to create laminated, definitive sockets, for the two additional prostheses. These sockets will be centrally fabricated at VANYHHS. The same materials as used in the subject's current socket will be used to create each additional socket to eliminate any variance in perceived weight or socket flexibility. Each additional socket will be aligned/programmed with a designated prosthetic foot to manufacturer's specifications by the study prosthetist.

